**Fig. 1 Fig1:**
[figure not shown]
Study design of the Care-On prospective observational trial

### Study population

Patients scheduled for or recently having undergone coronary artery bypass surgery (CABG), a fractional flow reserve test (FFR) and/or a percutaneous coronary intervention (PCI), an electrophysiology study (EP) and/or radiofrequency catheter ablation (RFCA), a transcatheter aortic valve implantation (TAVI), and/or valve surgery will be considered for participation. We will include a total of 100 patients. Patients included before their intervention will be monitored one week extra (the week prior to the intervention). A complete list of inclusion and exclusion criteria is provided in Table 1.

**Table 1 Tab1:** Inclusion and exclusion criteria for Care-On

***Inclusion criteria***	
***i***	Patients selected for or that underwent coronary artery bypass surgery (CABG), a fractional flow reserve test (FFR) and/or a percutaneous coronary intervention (PCI), an electrophysiological test (EFO) and/or radiofrequency catheter ablation (RFCA), a transcatheter aortic valve implantation (TAVI), and/or valve surgery
***ii***	Age ≥ 18 years
***iii***	Able to speak and read the Dutch language
***iv***	Willing and able to provide informed consent
***Exclusion criteria***	
***i***	No internet connection at home
***ii***	Not in possession of a computer or tablet; and mobile phone
***iii***	Not able or willing to wear activity tracker on a daily basis (for example due to work related obligations)
***iv***	Major planned (cardiac) surgery in the upcoming 3 months
***v***	Life expectancy < 1 year (e.g., severe renal disease, metastatic cancer)
***vi***	Physical impairments interfering with the lifestyle monitoring system, including not able to perform daily physical activities due to orthopedic or neurological disease, bed/chair ridden patients, visual impairments/blindness, severe cognitive disability
***vii***	Presence of wounds, injuries or infectious diseases on the skin where the wrist-wearable device(s) will be placed
***viii***	Mentally incompetent

After signing informed consent patients will receive instructions to use the lifestyle monitoring platform as part of the intake procedure with the researcher and nurse specialist. During this consultation patients will be instructed to use the platform on their personal computer and personal mobile phone. Patients will also receive a health watch, the Philips Health Band (PHB) (Health Band, Koninklijke Philips N.V. (KPNV), Amsterdam, The Netherlands).

### Design of the lifestyle monitoring system

We aim to develop a platform that can adequately monitor lifestyle behaviors of cardiac patients in an integrated and holistic manner. For each lifestyle domain (physical activity, sleep, nutrition and stress) we consulted domain experts to determine which method to use, what data to collect and in what frequency we would be able to gain sufficient insight in the patient's lifestyle behavior. Secondly, a systematic review is being conducted [15] on validated self-assessment tools for cardiovascular risk behavior. Based on these sources, we chose data collection methods and set a data collection scheme. We created a Minimum Viable Product (MVP) of the lifestyle monitoring system and tested the platform with seven researchers, two dieticians with the aim to go through several quick design cycles (one week uses). We asked one patient to test the system for 15 weeks (from October 2021 to February 2022) and to provide feedback over time. These combined insights were used to mature the lifestyle monitoring system to a study ready state.

### The lifestyle monitoring plan

The design process resulted in a combination of evidence-based monitoring methods and frequencies to monitor lifestyle efficiently, accurately, and with focus on the users’ needs.

#### Continuous lifestyle monitoring

Physical activity, daily nutrition intake, stress levels and sleep quality will be monitored continuously via the Care-On lifestyle monitoring system both objectively and subjective. The methods are displayed in Table 2.

**Table 2 Tab2:** Continuous lifestyle monitoring plan

**Lifestyle behaviour**	**Method**	**Subjective/objective**	**Minimum frequency per month/four weeks**
***Objective continuous lifestyle monitoring***			
Daily physical activity	24/7 activity monitoring via health watch (PHB)	Objective	Habitual physical activity 3–5 days of monitoring; sedentary: 5 days of monitoring [16]
***Subjective continuous lifestyle monitoring***			
Daily dietary habits and drinking behaviour	Self-report via chatbot based on 24 h food diary	Subjective	2–3 days of food records (preferably at least one weekday and one weekend day) [17]
Daily mental stress levels	Self-report via chatbot based on PANAS-scale (as Ecological Momentary Assessment (EMA) [18])	Subjective	No specific frequency, EMA can be adjusted to the design of the study
Daily sleep habits (quantity and quality)	Self-reported via chatbot based on Consensus Sleep Diary [19]; (additionally objectively via health watch)	Subjective (and objective)	At least 7 days including a weekend day [20] (Sleep diary); (5 nights for health watch [21])

The methods were combined in one scheme with a focus on minimizing patient burden and creating regularity. Therefore, the basis of the scheme consists of seven measurement days (based on the minimum habitual sleep measurement frequency, and this includes all days of the week). These seven measurement days are divided over two weeks (for 3 or 4 days per week (2 or 3 weekdays and 1 weekend day)) per four weeks to minimize the activity of the chatbot per week and include measurement free weeks (pause weeks). The first week of reporting contains four reporting days: Monday, Wednesday, Friday and Sunday. The second week of reporting contains three reporting days: Tuesday, Thursday and Saturday. The reporting weeks will take place every other week. Thus, in one month seven days (one complete week of reporting) of measurements is collected. Patients will be asked to wear the health watch in the weeks the chatbot is active to simplify the scheme. The chatbot and health watch scheme can be found in Table 3.

**Table 3 Tab3:** Continuous lifestyle monitoring scheme: “C” = day the chatbot is active. “Wear health watch” = patient is instructed to wear the health watch during the day (night is optional). In the row below the 'Week number' the days of the week are displayed from Monday (M) to Sunday (S)

Week 1							Week 2							Week 3							Week 4						
**M**	**T**	**W**	**T**	**F**	**S**	**S**	**M**	**T**	**W**	**T**	**F**	**S**	**S**	**M**	**T**	**W**	**T**	**F**	**S**	**S**	**M**	**T**	**W**	**T**	**F**	**S**	**S**
**C**		**C**		**C**		**C**									**C**		**C**		**C**								
Wear health watch							Pause							Wear health watch							Pause						

A description of the monitoring method and frequency of each lifestyle domain is described in the following sections.

##### Daily physical activity level

Daily physical activity will be measured using a health watch (the Philips Health Band (PHB)) [22]. The health watch measures: activity counts, heartrate, respiration rate, total energy expenditure, active energy expenditure, steps, activity type, amount of time the watch has been worn, resting heartrate, recovery heartrate, cardio fitness index and the amount of time a person was asleep or awake.

Patients are asked to wear the health watch for 2 weeks per month (Table 3) for at least 12 h a day, excluding periods for charging the device and periods where the device cannot be worn (such as during washing, showering and swimming).

##### Daily dietary habits and drinking habit

Eating habits and drinking habits are measured via the chatbot, for seven days per month (Table 3). Participants will be asked to complete a 24 h food diary. The chatbot will aid in filling in the food dairy by prompting the patients after breakfast, after lunch, after dinner and the following morning to fill in their nutrition intake. Patients are prompted to report on the following morning as well to capture whether the patient has eaten something after dinner and before going to bed.

Daily nutrition intake is based on the Dutch Dietary Guideline of 2015 [23] and the Eetscore Food Frequency Questionnaire (FFQ) [24], and assessed through the following categories: vegetables; fruit; legumes; nuts and peanuts; dairy, cheese and cream; bread, cereal products and potatoes; meat, meat substitutes and egg; fish and shellfish; butter, fat and oil; drinks; salt; soup; sugar and confectionery; cake and pastry, savoury snacks and fast food.

##### Daily mental stress levels

Daily self-reported mental stress levels are measured via the chatbot using Ecological Momentary Assessment (EMA) with questions derived on the Positive and Negative Affect Schedule (PANAS) [25]. The chatbot will ask participants to indicate their feelings 3 times per day (‘How did you feel over the past 10 min including now?’): at wake up, after lunch and after dinner (together with the nutrition notification). Participants are asked to what extent (on a 5-point Likert-scale: 0 = ‘very slightly or not at all’, 1 = ‘a little’, 2 = ‘moderately’, 3 = ‘quite a bit’ and 4 = ‘extremely’) they experience the following states: stressed, happy, irritated, anxious, active, whether they have control over what they do, feeling physically well (and if not, what is bothering them), a personalized stress symptom (the patient will be asked to provide this personalized stress symptom during first time use of the chatbot).

##### Daily sleep habits

Daily self-reported sleep quality and quantity is measured via the chatbot based on the Consensus Sleep Diary [19]. 5 items will be asked via the chatbot in the morning when the participant wakes up, with the following outcomes: usual bedtime (time), usual getting up time (time), hours of sleep per night (hours), perceived quality of sleep (Likert-scale), perceived feeling of restfulness (Likert-scale). Secondly, the PHB will objectively measure sleep quantity and quality.

#### Periodic lifestyle assessment

Patients will be asked to fill in a set of questionnaires (quarterly assessment) at baseline (t0) (one week before intervention), one week after discharge (t1) and at 3 months (t2), 6 month (t3), 9 months (t4) and 12 months after discharge (t5). The results of  the questionnaires related to the patients lifestyle (as described in Table 4) are visualized with a score in the lifestyle monitoring system.

**Table 4 Tab4:** Periodic lifestyle assessment overview

*Periodic lifestyle assessments (quarterly)*		
**Lifestyle parameter**	**Questionnaire**	**Objective**
Perceived physical fitness	FitMáx	The FitMáx [26] used to assess perceived physical fitness as an addition to the daily physical activity data measured by the PHB
Diet quality	NutriMáx (custom FFQ)	A customized healthy diet assessment questionnaire, the NutriMáx (a custom questionnaire based on Dutch Dietary Guideline [23]) is used to assess diet quality and nutrition behavior as an addition to the daily eating habits
Smoking status	Custom questionnaire	The participants will be asked to indicate their smoking status and average amount of smoking (cigarettes per day)
Perceived mental stress	Perceived Stress Scale (PSS-10)	The PSS-10 [27] is used to assess perceived mental stress as an addition to the daily stress level measurements
Perceived sleep quality	Pittsburgh Sleep Quality Index (PSQI)	The PSQI [28] is used to assess perceived sleep quality

### The lifestyle monitoring system for patients

Patients will receive an account for the Care-On lifestyle monitoring system for administering daily health data. The patients will be asked to install the application of the platform (MijnFlowCoach [29]) on their mobile phone or tablet and get additional instructions to access the platform on their desktop.

The Care-On platform for lifestyle monitoring contains five main features:**Health watch (PHB) integration:** Upload and review daily physical activity data collected via an integrated wrist-worn wearable device.**Chatbot module:** The chatbot module will prompt the patients to self-report on their lifestyle behaviour regarding mental stress, nutrition intake and sleep habits.
Measuring daily dietary habits and drinking habitMeasuring daily mental stressMeasuring daily sleeping habits**A personal dashboard:** A personal dashboard will give feedback on the patients’ adherence to self-report their lifestyle behaviour and provide an overview of the self-reported lifestyle data. Secondly, every quarter patients will be asked to fill in more extensive questionnaires on lifestyle parameters as an addition to the daily chatbot and smartwatch integration measurements via the personal dashboard.**A goal tracking module:** The patient has the option to set and monitor monthly goals with the goals tracking module.

An impression is shown in Fig. 2.

**Fig. 2 Fig2:**
[figure not shown]
Care-On lifestyle monitoring system with integrated health watch and lifestyle chatbot

#### Health watch

The PHB will be integrated in the platform and data visualizations of the data collected with the watch will be visualized on a personal dashboard. The patient will not be treated or coached based on the parameters measured by the devices as caretakers do not have access to these data. The patient will wear the device during a period of one week before intervention (if possible) and one year after intervention. After this period the patient will hand in the devices.

Patients are instructed to wear the PHB at least 12 h per day. The PHB will be paired with the mobile phone of the patient via the ‘Philips Gezondheid band’ application [30] which will be installed on the patient's phone at first visit. The patient is instructed to open the application to synchronize the data of the watch with the Philips-application once every two days. The application will provide the patients with data visualizations of the data collected by the PHB. The patients may wear the PHB continuously (also in weeks of no chatbot measurements) and during the night by choice.

#### Chatbot

A conversational agent (chatbot), called ‘Caro’, is integrated in the Care-On platform. Caro is represented by a female avatar and is programmed to ask the patients questions to monitor the lifestyle parameters sleep, stress, and nutrition intake.

During a measurement day Caro starts a chat session five times per measurement day: in the morning (sleep and stress), after breakfast (nutrition), after lunch (stress and nutrition) and after dinner (stress and nutrition) and the morning after (nutrition). During onboarding Caro will ask patients to fill in their daily schedule to personalize the chat timers.

If a patient is not able to answer a question directly, Caro will ask again after 30 min. The patient has until the next chat session to answer the questions. If a patient has answered all questions of the chat session the measurement is completed and counted for compliance.

The chatbot is available via the platform on desktop and via the ‘MijnFlowCoach’-application [29] which is installed on the patient's phone during onboarding. An impression is shown in Fig. 3.

**Fig. 3 Fig3:**
[figure not shown]
Example of chatbot (Caro) questions regarding sleep quantity and quality

#### Personal dashboard

The data acquired via the PHB, the chatbot and the periodic lifestyle assessments are visualized and accessible for the patient in a dashboard in the lifestyle monitoring system. The data visualized on the dashboard is focused on the adherence to delivering self-reported data to the system and the content of their delivered data. An example is shown in Fig. 4.

**Fig. 4 Fig4:**
[figure not shown]
Personal dashboard: nutrition overview including visualized lifestyle goals

The periodic lifestyle assessments are also available via the dashboard. After having completed the periodic lifestyle assessment basic advice on the results is shown in the dashboard.

#### Goal tracking module

The patient has the option to set and monitor monthly goals with the goal tracking module. This module is optional. Default goals for dietary intake and physical activity will be provided based on the Dutch Dietary Guideline of 2015 and Dutch Physical Activity Guideline of 2017 [31]. The default goals for sleep and stress are based on the advice given by the Dutch General Practitioners Associations (in Dutch ‘Nederlands Huisartsen Genootschap (NHG)’) on the ‘Thuisarts’-website [32, 33]. The patient has the option to alter the default goals to fit their personal situation.

#### Quarterly consults by research nurse and final evaluation

Every quarter the research nurse will contact the patient via phone consultation to ask whether the patient has problems using the system. Secondly, the research nurse will ask for brief feedback on the use of the system. Thirdly, the research nurse will remind the patient to fill in the quarterly assessment when the patient has not completed it yet. At last, the research nurse will ask the patient to report medical events.

Within two weeks after the trial period has ended the SUS will be administered again and a semi-structured interview will be held with the participant to discuss their experience with the lifestyle monitoring system. During the semi-structure interview the following topics will be discussed: their quality of life after intervention, their experience with cardiac rehabilitation and/or cardiac care after intervention, their experience with the Care-On study in general, and their perceived usability of the different functionalities of the lifestyle monitoring system.

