##### Adherence classification and dropout threshold

Classifications for low, moderate and high adherence are set up to monitor patient’s compliance with providing lifestyle data. The health watch adherence rate, chatbot adherence rate and quarterly assessment completion rates make one-third of the general adherence rate:

$$general\,adherence\,rate\,=\,\left(adherence\,rate\,PHB\,+\,adherence\,rate\,chatbot\,+\,quarterly\,assessment\,completion\,rate\right)/3$$

The chatbot compliance rate is based on the minimum number of days of data collection necessary to gain insight in habitual intake of commonly consumed food. The minimum number of days of data to be collected to gain insight in habitual intake of commonly consumed food is 2–3 days (of food records, real-time monitoring) [17]. Thus, if a patient fills in at least 50% of the measurements, the minimum number of days is certainly met.

The health watch compliance rate is based on the minimum number of days necessary to gain insight in habitual physical activity and sedentary behavior. Previous studies [16] indicate that 3–5 days of monitoring is necessary to assess habitual PA and for sedentary behavior 5-days of monitoring will provide a reliable estimate. Patients were instructed to wear the PHB for at least 12 h a day on average during measurement weeks. Thus, if a patient wears the watch at least 50% of the prescribed time, the minimum number of days certainly is met.

The quarterly lifestyle assessment completion rate is based on the amount of completed quarterly assessments.

The adherence to providing self-tracking data is evaluated by the researchers every four weeks per patient. The total adherence score is a combined score of the chatbot adherence, activity tracker wear adherence and quarterly assessment adherence. The levels are as follows:Low adherence classification: The patient's adherence is below 50% measured over a 4-week interval.Moderate adherence classification: The patient's adherence is between 50 and 75% measured over a 4-week interval.High adherence: The patient’s adherence is above 75% measured over a 4-week interval.

Patients who have a general adherence rate below 50% will be contacted and stimulated to resume using the system by the research nurse once; if patients did not resume after 1 month they are classified as non-adherent.

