#### Secondary endpoints

The secondary endpoints are:Usability (measured using the SUS, the feedback given by the patients during the phone consults with the research nurse, the quarterly questionnaires and the evaluation interview) and the success rate (percentage of tasks that the patients complete correctly)).Predictors of adherence to the lifestyle monitoring system (demographic and disease characteristics, quality of life, self-efficacy, depressive symptoms and anxiety, motivation, stage of change, fatigue, physical fitness, levels of metal stress, use of a goal tracking functionality, perception of system usability and prior experience with technology. Standardized questionnaires will be used for self-report measures and objective ambulatory measures from the lifestyle monitoring system for objective lifestyle measures).The association between lifestyle behaviour at baseline with clinical outcomes will be examined by evaluating patient clinical records (re-hospitalizations related to cardiac disease) and standardized self-report data (quality of life).

The data will be analyzed using multiple regression analysis. An overview of the questionnaires to be complete by the patients per timepoint for the secondary endpoints is shown in Table 5.

**Table 5 Tab5:** Overview of the assessments of the secondary endpoints of the Care-On study

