		**STUDY PERIOD**						
		Baseline	Rehabilitation					Evaluation
***TIMEPOINT***		***-t1***	***t1***^***2***^	***t2***	***t3***	***t4***	***t5***	***t6***
*Predictors of adherence*								
Health-related Quality of Life	Short Form Health Survey (SF-12) v1 [34]	x	x	x	x	x	x	
Self-efficacy	General Self-Efficacy Scale (GSES) [35]	x						
Depressive symptoms and anxiety	Hospital Anxiety and Depression Scale (HADS) [36]	x						
Motivation and Stage of Change	Readiness-to-Change Lifestyle Questionnaire and Confidence-to-Change Lifestyle Questionnaire [37]	x						
Fatigue	Fatigue Assessment Scale (FAS) [38]	x						
Physical fitness^1^	FitMáx [26]	x	x	x	x	x	x	
Levels of mental stress^1^	PSS-10 [27]	x	x	x	x	x	x	
System usability	SUS [39]	x						x
Mobile Device Proficiency	Mobile Device Proficiency Questionnaire (MDPQ)-16 [40]	x						
*Clinical data*								
Medication adherence	General Adherence Scale (GAS) [41]	x	x	x	x	x	x	
*Usability*								
Satisfaction and usability	Custom questionnaire based on the customer satisfaction score (CSAT) [42] and single ease questions (SEQ) [43]		x	x	x	x	x	
Self-report chatbot and activity tracker usage	Custom questionnaire based on GAS		x	x	x	x	x	

^1^These questionnaires are also part of the periodic lifestyle assessment

^2^The questionnaires of 't1' will not be asked when a patient is included after intervention

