### Sample size calculation and statistical analysis

The sample size is based on the primary objective adherence. Anticipating a dropout rate of 50% at 1 year follow up, 100 patients are needed to estimate this adherence rate with a precision of ± 10% (95% CI = [0.398, 0.601]).

Descriptive statistics will be used to report demographics and baseline characteristics. The primary outcome (i.e., ‘adherence’ based on continued use status at 1-year follow-up) will be analysed as a dichotomous outcome measure. Predictors of adherence status and which factors predict re-hospitalizations related to cardiac disease (i.e., the secondary aims) will be investigated using multiple logistic regression analyses. Predictors continuous outcome measures (e.g., QoL) will be examined using linear regression models. Analysis will be carried out in the statistical software package SPSS (version 24, SPSS Inc.).

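### The only SUS after sustained use is taken after the trial year, with 50% dropout expected, so it is likely to describe mainly completers and may overstate usability for all starters

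*Protocol article*

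**What the plan says.** In the Protocol article, the section on quarterly consults and final evaluation places the second SUS after the year of use: "Within two weeks after the trial period has ended the SUS will be administered again". A semi-structured interview is held at the same point.

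Table 5 agrees. Its row "System usability", which stands under the predictors of adherence, has crosses at baseline (labelled -t1) and at t6, and none from t1 to t5.

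The Secondary endpoints section lists usability first: "Usability (measured using the SUS", together with feedback from the nurse's calls, the quarterly questionnaires, the evaluation interview and the success rate. The same section names perceived system usability as a candidate predictor of adherence. Table 5 also schedules a custom usability questionnaire, based on the CSAT and SEQ, at t1 to t5. A footnote drops t1 for patients included after their intervention.

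On attrition, the sample size section states "Anticipating a dropout rate of 50% at 1 year follow up". Patients whose general adherence rate is below 50% are contacted once by the research nurse, and "if patients did not resume after 1 month they are classified as non-adherent". No usability measure is attached to that contact.

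**The concern.** The SUS taken at baseline can reflect onboarding and at most the first days of use. The SUS taken at t6 is the only one informed by sustained use, and by then the plan expects about half of those who started to have gone. The trial itself treats perceived usability as a possible driver of adherence. If it is one, a score obtained mainly from people who adhered has been selected on its own consequence, and the natural direction of the error is upward.

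There is a second problem of timing. Adherence is completion at one year, and the t6 SUS is taken after that is settled. It cannot be a prospective predictor. If only completers answered, adherence would not vary among the respondents and no association could be estimated at all.

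What is at stake is the reading of the first-listed secondary endpoint. A SUS that was never collected from those who left cannot be recovered in the analysis.

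**Working it through.** **Inputs from the article**
- Planned sample: 100 (Study population: "We will include a total of 100 patients").
- Dropout at one year: d = 0.50 (Sample size calculation and statistical analysis).
- SUS timing: baseline and t6 only (Table 5; quarterly consults and final evaluation).

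**Inputs that are assumptions**
- r: the share of drop-outs who still answer the SUS at t6, taken as 0, 0.25, 0.50 and 1.
- D: mean SUS of completers minus mean SUS of drop-outs, taken as 5, 10 and 20 points on the 0 to 100 scale.

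**Step 1. The plan's own figure.** The article gives a "precision of ± 10% (95% CI = [0.398, 0.601"]. For a proportion of 0.50 and a half-width of 0.10, n = 1.96² × 0.25 / 0.10² = 96.04, so 97, close to the planned 100. The exact (Clopper-Pearson) 95% interval for 50 of 100 is 0.3983 to 0.6017. This is the stated interval, with the upper limit cut rather than rounded. The 50% is therefore the figure on which the trial was sized, and it is a fair basis here.

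**Step 2. Who answers at t6.** Completers: 100 × (1 − d) = 50. Drop-outs who answer: 100 × d × r = 50r. Respondents: 50 + 50r. Share of completers: 50 / (50 + 50r).

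**Step 3. Overstatement of the t6 mean.** Measure from the completer mean.
- Mean of all starters: −dD.
- Mean of respondents: −D × dr / [(1 − d) + dr].
- Difference, respondents minus all starters: D × d(1 − d)(1 − r) / [(1 − d) + dr].

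For d = 0.50, r = 0.25 and D = 10: 10 × 0.25 × 0.75 / 0.625 = 3.0 points.

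| Drop-outs answering (r) | Respondents | Share completers | D = 5 | D = 10 | D = 20 |
|---|---|---|---|---|---|
| 0% | 50 | 100% | 2.5 | 5.0 | 10.0 |
| 25% | 62.5 | 80% | 1.5 | 3.0 | 6.0 |
| 50% | 75 | 67% | 0.8 | 1.7 | 3.3 |
| 100% | 100 | 50% | 0 | 0 | 0 |

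If the two groups rate the system alike (D = 0), the difference is zero in every row.

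**Step 4. What the other sources add.** The CSAT/SEQ questionnaire at t1 to t5 is a different instrument from the SUS. Patients included after the intervention skip t1, so one who stops before t2, at three months, reaches no scheduled usability questionnaire during use. The calls collect brief feedback, with no scale named. The success rate counts tasks done correctly, which is not perceived usability.

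**The case against.** The strongest reply is that the usability endpoint is wider than the SUS, and this stands. The nurse starts the quarterly calls and asks about problems and experience, whether or not the patient opens the platform. A participant who stops in month 7 was already due to complete the CSAT/SEQ items at three and six months. A reader might infer that the whole endpoint rests on completers; the article does not support that.

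Three other tempting inferences also fail.
- *Non-adherent patients necessarily lack the quarterly questionnaires.* The general adherence rate is the mean of three rates. A patient at 20% for the watch, 20% for the chatbot and 100% for the quarterly assessments scores (20 + 20 + 100) / 3 = 46.7%, below the threshold with every assessment completed.
- *The t6 SUS is confined to completers and will be overstated.* The article does not restrict it, and people who have stopped using the system may still be reachable. Neither r nor D is given.
- *The trial cannot show whether poor usability leads to dropout.* The baseline SUS, the CSAT/SEQ items and the calls all come before later dropout. Only the t6 score is ruled out as a prospective predictor.

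It can also be said that exit procedures are a detail a condensed article leaves to the full protocol. That would excuse silence about procedure. But the SUS schedule itself is stated, in both text and table, and can be judged as stated.

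**Conclusion.** The concern holds in a limited form. Followed as written, the schedule leaves the only SUS after sustained use, and the interview, mainly to completers: 67% to 100% of respondents if at most half of the drop-outs answer. That score is at risk of overstating usability for all starters. For an assumed 10-point gap the excess is 5.0, 3.0 or 1.7 points when 0%, 25% or 50% of drop-outs answer, and it vanishes if all answer or if the groups rate alike. These figures are illustrations and not estimates of bias in this trial. They rest on the plan's 50% dropout and on values of r and D that the article does not give.

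Separately, and without any assumption, the t6 SUS comes after the adherence outcome and cannot predict it prospectively. The other usability sources soften the first problem but thin out with dropout and do not supply a SUS. This is a low-cost improvement to one component of a secondary endpoint; the primary outcome and the sample size are unaffected.

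**What to change.** Give the 10-item SUS when a participant stops or is contacted for adherence below 50%, within the call the nurse already makes.

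In the report:
- give the last on-use SUS for all starters who have one, and separately for completers and non-completers;
- give the t6 response rate by completion status;
- describe the t6 mean as applying to its respondents;
- do not use the t6 score as a prospective predictor of adherence.

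The cost is a few minutes per call and one table. Some who stop will decline, and the mode and timing of administration will be mixed, so comparisons between the groups need that caution. If data collection has already closed, the reporting items can still be done.
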